**Figure 1 F1:**
[figure not shown]
CONSORT diagram.

### Interventions

#### MEmory Specificity Training

MEST is the training package developed by [name] and colleagues, used in the first pilot study of memory specificity training
[24]. For the current study, the original treatment manual was translated from Dutch into English, and, in collaboration with the treatment developer, has been extended from four to five sessions, as used in our pilot RCT
[25]. It consists of a fully manualised, structured treatment delivered over five 60-minute sessions to groups of 5 to 8 individuals. The treatment aims to enhance memory specificity through the systematic practice of memory retrieval in response to emotional and neutral cue words. This practice takes place both during the sessions and at home.

The first session involves providing basic psycho-education about depressive symptoms and memory difficulties common in depression. As a group, participants then practice recalling memories in response to positive and neutral cues, with demonstrations and support from the therapists. For homework, participants have to identify specific memories in response to ten cue words, and identify an additional ‘memory of the day’ each day. The second session follows the same format with further practice. For homework, participants must identify specific memories in response to ten cue words, and identify two further daily specific memories. In the third session, practice in response to negative cues (as well as positive cues) is introduced, and homework is identical to that following Session 2. Session 4 involves practice to positive, negative, and neutral cues and also includes an example of noticing overgeneral thinking in everyday contexts. For homework, participants identify memories in response to ten cues, identify a single ‘memory of the day’ each day, and provide a daily example of when they have noticed themselves thinking in an overgeneral fashion. The final session involves further practice and revision of the material covered throughout the treatment.

#### Education and support

The ES intervention will follow the same format and length as the MEST intervention (that is, delivered to groups of 5 to 8 individuals over five 60-minute sessions). ES has been manualised for this trial and is a cognitively-orientated intervention. The aim is to provide a non-judgemental, supportive environment in which participants are encouraged to raise and discuss a range of events that occur each week. These events may be positive, negative, or benign and non-emotional in nature: it is up the individuals to bring to the group whatever they would like. Through reflection and discussion, the goal is to support and help individuals attain optimal adjustment and to better cope with everyday life. This approach draws on the supportive aspects of the therapeutic relationship to assist with more effective psychological functioning, with input from other group members. It is a non-directive intervention whereby therapists do not use directive methods such as cognitive-behavioural techniques (for example, Socratic questioning, cognitive restructuring, behavioural experimentation).

The rationale for choosing an education and support comparison group over more traditional psychological approaches (for example, supportive counselling, CBT) was to ensure that the content covered by the two interventions is as similar as possible. More traditional approaches tend to focus on distressing and emotional material, which is not the focus of the MEST intervention. Therefore, to optimise equivalence in content between the groups we decided to take a cognitive approach and ask people to record material from each week that can be positive, negative or neutral. The role of the group is to then help individuals to notice patterns in their responses and adopt a self-reflective approach, which may improve psychological functioning.

In the first session, psycho-education about depressive symptoms is presented and the experience of group members is normalised. Participants are invited to share why they have decided to participate in this study. An outline of the programme is then provided and participants are informed about how to complete the homework daily diary where they note down a significant event that occurred each day, which can be shared in the following session. The second session involves reviewing the homework and continued discussion of events that participants have noted down in their diaries. These discussions are led by the therapists, but as with the MEST intervention, input from other group members is encouraged. Sessions 3, 4, and 5, follow an identical structure - a homework review, followed by discussion and support, with the homework task to record a positive, negative or neutral daily event for discussion at the next session. The final session does not require completion of homework tasks. The ES manual was developed by two clinical psychologists ([name] and [name]), in consultation with two experienced counsellors from the Cambridge area.

#### Treatment integrity

Two clinical psychologists with experience in treating adult depression will deliver the MEST and ES interventions. Treatment fidelity and clinician adherence will be established using continued monitoring and through independent rating. After every session, clinicians will complete the Treatment Fidelity Checklist, which is a session-by-session measure of compliance with the protocol, and these will be evaluated during weekly clinical supervision with the trial lead. In addition, a random 25% of the audio-taped treatment sessions will be rated for adherence to the manuals by an experienced clinician, independent of the core trial team. Homework completion will be monitored and assessed using self-report questionnaire measures.

### Measures

#### Primary outcomes

The primary outcome measure will be depressive symptoms at 3-month follow-up using the well-established, psychometrically sound self-report measure, the Beck Depression Inventory II (BDI-II)
[31].

#### Secondary outcomes

Secondary outcomes will be depressive diagnostic status and depression-free days since the beginning of treatment at the post, 3-month and 6-month (MEST group only) follow-up assessment as measured by the Longitudinal Interval Follow-up Evaluation (a form of the Structured Clinical Interview for DSM-V, which is the gold standard for diagnostic assessment)
[33]; depressive symptoms at post-treatment and 6-month follow-up (as measured by the BDI-II); and memory specificity at post and 3-month follow-up, as measured by the gold standard in memory specificity research, the AMT
[32].

#### Process measures

To address our explanatory question concerning the mechanisms by which MEST improves outcomes in depression, we include a number of process-related tasks, parallel forms of which will be administered at baseline, at post-intervention, and at 3-month follow-up, across the trial arms. Accordingly, change on theoretically-derived processes from pre- to post-treatment (outlined below) will be used to predict treatment outcome at follow-up using mediational analyses
[34]. Derived from theory and evidence, we will examine whether the effect of MEST on treatment outcome is mediated by changes in memory specificity, interpersonal problem solving, rumination, cognitive avoidance, and executive control. Problem-solving will be measured using a shortened version of the Means-Ends Problem Solving task
[35], which has been used previously in clinical research. Rumination and cognitive avoidance will be measured using the psychometrically valid gold-standard self-report measures for each construct - the Rumination Response Scale (RRS)
[36] and the Cognitive Avoidance Questionnaire
[37]. Executive control will be indexed via verbal fluency and working memory measures commonly used in neuropsychological assessment
[38].

### Methodological aspects

#### Power analysis and sample size

Although a standard power calculation based on detecting treatment effects would be the conventional approach to determining sample sizes for clinical trials, the main aim of the current exploratory trial is to investigate the efficacy, acceptability and feasibility of MEST, in preparation for scaled up later phase evaluations of the intervention in line with MRC guidance. Our previous experience with Phase II exploratory trial platforms indicates that 60 participants (30 in each arm) will provide sufficient numbers to evaluate outcome, feasibility and acceptability, and to generate preliminary process data for this treatment. This sample size will give 24 patients in each arm if we allow for 20% attrition. This will provide a plausible range of point estimates of effect on our set of outcome measures sufficient to guide us in sample size calculations for later phase trial work.

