### Participant allocation

Eligible participants will be cluster randomised using a blocked randomisation procedure with 5 to 8 participants in a group to receive the intervention. This will be achieved using computer-generated, quasi-random numbers and will be conducted by the trial statistician ([name]), blind to study objectives. Once generated, this information is passed to the trial lead ([name]), who informs the project coordinator responsible for delivering the intervention ([name]) within 48-hours of the commencement of a given group.Figure 
1 summarises the trial CONSORT (consolidated standards for reporting trials) diagram. Following randomisation, patients are offered treatment for five consecutive weeks (commencing within four weeks of the baseline assessment).

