#### Statistical analysis plan

Initial analyses of the primary and secondary outcomes will be conducted by the trial statistician, following CONSORT standards (there are no planned interim analyses). Multiple imputation will be used to handle missing data. Initial analyses will be conducted on an intention-to-treat basis, with subsequent analyses being per protocol. Mixed model analyses of variance (ANOVAs) will be used to compare groups at the four assessment points - baseline, post-intervention, 3-month follow-up, and 6-month follow-up on primary and secondary outcomes, as appropriate. Baseline levels on relevant measures will be included as covariates, as appropriate. Mediational analyses following the Kraemer recommendations
[34] will investigate hypothesised mechanisms of change across the trial arms.

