## Discussion

According to the World Health Organisation
[1], depression is major global burden of disease and, by 2020, will be the second leading cause of world disability. Depression affects people in all communities across the world, making it a matter of global concern from health, social and economic perspectives. Fortunately, evidence-based treatments that work such as cognitive-behavioural therapies are available. However, these treatments are not always accessible to those who need them, and the treatments themselves are expensive to deliver. There has been a growing recognition of the need to develop cost-effective interventions that can be delivered in a stepped care model, supported by a number of government initiatives (particularly in the UK). The underlying goal is to make evidence-based interventions more accessible and affordable (for example, NHS internet-based CBT, IAPT). The proposed RCT is in line with this objective.

The two pilot trials that have been conducted suggest that MEST, if efficacious in the treatment of depression, may offer a cost-effective, brief, low-intensity intervention with potential for cross-cultural application. For example, one of the pilot studies was conducted with Afghan refugees in Iran, the other in an inpatient sample in Belgium. This is of particular interest given that risk factors for depression include economic and social disadvantage
[40] and those in impoverished communities have greater difficulty accessing health care
[41]. If acceptability, feasibility, and superiority to the ES control can be demonstrated, the results from this trial will support the need for a fully powered Phase III definitive trial to examine MEST as a treatment for mild to moderately depressed individuals. We anticipate that MEST may be used as an adjunct or precursor to more comprehensive therapies such as CBT. It is possible that MEST may have utility in reducing symptoms to a level where patients are able to engage in more demanding therapies such as CBT. Results of this trial will also indicate whether there is potential for MEST to be used as a stand-alone treatment for depression. Further, we expect that the idiosyncratic nature of MEST may appeal to particular patient groups who do not wish to address emotional content. Finally, the embedded process study will enable us to better understand the mechanisms driving the therapeutic effects of the treatment.

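### With 24 per arm, the MEST–ES effect estimate is too imprecise to guide the size of a later trial, contrary to what the sample-size section says

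*Protocol article*

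**What the plan says.** All of this is in the protocol article. The section on power analysis and sample size acknowledges the usual route ("Although a standard power calculation based on detecting treatment effects would be the conventional approach to determining sample sizes for clinical trials") and then declines it because the trial is exploratory. Its reasons for the size are experience with similar trials, from which "60 participants (30 in each arm) will provide sufficient numbers to evaluate outcome, feasibility and acceptability", and the generation of preliminary process data. It then gives the retained number: "This sample size will give 24 patients in each arm if we allow for 20% attrition". From that number it draws the conclusion at issue: "This will provide a plausible range of point estimates of effect on our set of outcome measures sufficient to guide us in sample size calculations".

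Three other places bear on it:
- The primary outcome section fixes the main comparison: "The primary outcome measure will be depressive symptoms at 3-month follow-up", measured by the BDI-II.
- Participant allocation says "Eligible participants will be cluster randomised using a blocked randomisation procedure with 5 to 8 participants in a group".
- The statistical analysis section says "Baseline levels on relevant measures will be included as covariates, as appropriate".

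The article gives no interval width, SD, important difference or intracluster correlation (ICC).

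**The concern.** An exploratory trial need not be powered, and declining a power calculation is not the problem. The problem is that the section asserts a different, checkable property: that the effect estimates from 24 per arm are good enough to inform the next trial's sample size. The quantity named is the effect, not the SD, attrition or clustering.

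Required sample size varies with the inverse square of the planning effect, so an imprecise effect produces very large swings in the size derived from it. If the sentence is acted on, the next trial could be far too small to detect a real benefit, or so large that it is never run. Randomising groups of 5 to 8 makes the estimate less precise than 24 independent patients per arm would suggest, and the section makes no allowance for this.

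**Working it through.** **Inputs from the article.** 30 per arm; 20% attrition; groups of 5 to 8; continuous primary outcome.

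**Assumptions (the article gives none of these).** SD = 1, so results are in SD units; two-sided 95% intervals; later trial at 80% power and two-sided 5%; true effect 0.5 SD for illustration; design effect (DE) 1.0 to 1.4; baseline-to-outcome correlation r from 0 to 0.7.

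**1. The plan's own figure.** 30 × (1 − 0.20) = 24 per arm. It reproduces.

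**2. Precision of the difference.** SE = √[(2/24) × DE × (1 − r²)]; half-width = t(0.975, 46 df) × SE = 2.013 × SE.

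| DE | r | SE | 95% half-width |
|---|---|---|---|
| 1.0 | 0 | 0.289 | 0.58 |
| 1.2 | 0 | 0.316 | 0.64 |
| 1.4 | 0 | 0.342 | 0.69 |
| 1.0 | 0.5 | 0.250 | 0.50 |

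DE 1.2 corresponds, for example, to ICC 0.04 in groups of 6: 1 + 5 × 0.04. Groups of 5 to 8 mean only about 4 to 6 groups per arm (30/8 to 30/5). If the critical value reflects about 10 groups in all (8 df, t = 2.306), the half-width at DE 1.2 and r = 0 is 2.306 × 0.316 = 0.73.

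**3. What the estimate implies for the next trial.** Later n per arm = 2 × (2.802/d)², where d is the planning effect. At the true 0.5 SD this is 2 × (2.802/0.5)² = 63. With DE 1 and r = 0 in the present trial:
- Middle half of estimates: 0.5 ± 0.674 × 0.289 = 0.305 to 0.695, giving 169 down to 33 per arm.
- 10th to 90th percentile: 0.5 ± 1.282 × 0.289 = 0.130 to 0.870, giving about 929 down to 21 per arm.

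For the same 10th to 90th percentile range, r = 0.5 gives about 487 down to 23, and r = 0.7 gives 282 down to 27, still about tenfold.

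**4. How often the next trial would be badly underpowered.** Its true power falls below 50% when 0.5 × √(n/2) < 1.96. That happens when the observed effect exceeds 0.5 × 2.802/1.96 = 0.715. The probability is 1 − Φ((0.715 − 0.5)/0.289) = 0.229. Dividing by the chance of a positive estimate, Φ(0.5/0.289) = 0.958, gives 0.24.

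**5. What the interval shows if MEST has no effect.** P(upper limit ≥ d) = 1 − Φ((d − half-width)/SE). With DE 1, the interval still reaches a benefit of 0.3 SD in 83% of trials at r = 0 and 71% at r = 0.7. For 0.5 SD the figures are 61% and 34%.

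**6. What the trial does estimate usefully.** The pooled SD on 46 df has a 95% interval of 0.83 to 1.26 times its estimate. Attrition of 20% in 60 has one of 0.20 ± 1.96 × √(0.2 × 0.8/60), or about 10% to 30%.

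**The case against.** The best defence is that the sentence is modest. It speaks of guidance, not of putting the observed primary effect into a formula, and it does not exclude an important difference, an SD or an attrition rate as inputs. The trial is openly exploratory, its size also rests on feasibility, acceptability and process data, and sizing the next trial is a matter for that trial's protocol. Much of this stands: step 3 models the most direct use of the estimate, and the other reasons for 60 are untouched. But the sentence calls the effect estimates sufficient and names no other input, so it invites that use.

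Baseline adjustment is planned where appropriate and does help, but the implied sizes still span about tenfold at a correlation of 0.7.

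Three stronger readings are tempting but not supported:
- **That the trial cannot justify a definitive trial, or that an ineffective MEST would usually lead to one.** The Discussion sets a different condition: "If acceptability, feasibility, and superiority to the ES control can be demonstrated, the results from this trial will support the need". An interval that merely reaches a useful effect does not meet it, and with valid inference a null treatment would show superiority only about 2.5% of the time. The weakness under that rule is the reverse: power at 0.5 SD is Φ(0.5/0.289 − 1.96), about 41%.
- **That the share of later trials below 80% power condemns this sample size.** That share is about half for any unbiased estimate, however large the first trial.
- **That under no effect the interval would usually include any useful benefit.** This is robust for 0.3 SD only. For 0.5 SD it fails under strong baseline adjustment.

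**Conclusion.** The point holds in a limited form. The sufficiency statement is unsupported and, for the effect estimate, wrong. The 95% half-width is roughly 0.5 to 0.7 SD over the main cases tabulated, and a true effect of 0.5 SD could plausibly be turned into a next trial of anywhere from about 20 to more than 900 per arm. About one in four later trials sized on a positive estimate would have less than 50% power.

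These sizes rest on the assumed 95% level, true effect, design effect and correlation. The order of magnitude of the swing does not depend on the particular choice of correlation or ICC. The conclusion concerns the effect estimate only: the SD and attrition can inform later planning, and the feasibility aims are not in question.

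**What to change.** In the sample-size section, replace the sufficiency sentence with the expected precision. For example: 24 per arm gives a 95% interval of about ±0.6 SD for the 3-month BDI-II difference, wider once the randomised groups of 5 to 8 are allowed for, and this is too wide to set the effect size for a later trial.

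Then state that:
- the later trial will be sized on a prespecified BDI-II difference judged clinically important;
- this trial will supply the BDI-II SD, baseline-to-follow-up correlation, attrition and feasibility, with a range of assumed ICCs, since about 4 to 6 groups per arm cannot fix the ICC;
- the observed effect will be reported with its interval and not used as the planning effect.

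The cost is wording only, with no more patients or data. The drawback is that the case for 60 participants looks less favourable, although feasibility, acceptability and process data remain as reasons.

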#### Data collection

Outcome data will be collected on site at three assessment points (baseline, post-treatment, and 3-month follow-up). Outcome data on all participants who are randomised will be collected if possible and with appropriate consent. At 6-month follow-up, participants from the MEST arm will be contacted by phone and administered the Longitudinal Interval Follow-Up Evaluation to ascertain depression-free days (a form of the SCID-IV), and will be asked to complete the BDI-II electronically. Memory specificity and the full process battery will not be administered at the 6-month follow-up. Data will be stored securely at this site under the management of the trial coordinator ([name]). Spot checks on data entry will be performed to promote data quality.

#### Blinding

Outcome assessments are conducted by independent raters who have no therapeutic relationship with the patients and are blind to treatment condition. Double blinding of patients and therapists is not possible due to the nature of the trial (that is, a psychological intervention). Under no circumstance will unblinding be necessary since participants and therapists are not blinded to intervention allocation.

#### Statistical analysis plan

Initial analyses of the primary and secondary outcomes will be conducted by the trial statistician, following CONSORT standards (there are no planned interim analyses). Multiple imputation will be used to handle missing data. Initial analyses will be conducted on an intention-to-treat basis, with subsequent analyses being per protocol. Mixed model analyses of variance (ANOVAs) will be used to compare groups at the four assessment points - baseline, post-intervention, 3-month follow-up, and 6-month follow-up on primary and secondary outcomes, as appropriate. Baseline levels on relevant measures will be included as covariates, as appropriate. Mediational analyses following the Kraemer recommendations
[34] will investigate hypothesised mechanisms of change across the trial arms.

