## Methods/Design

### Study design

The design is a single-blind, parallel cluster RCT comparing MEST to an ES intervention, with an embedded mechanism study. The intervention duration is equivalent in both conditions and participants will be assessed four times - at baseline, at post-treatment, and at 3-month and 6-month follow-up time points. The first three assessment points (that is, baseline, post, and 3-month follow-up) are face-to-face and include the full battery of assessment measures, including primary and secondary outcomes and process measures. Assessment at 6 months will be for the MEST group only and will take place via phone. This final assessment includes primary and secondary outcomes only (with the exception of the Autobiographical Memory Test; AMT).

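### Therapy groups are randomised, but the stated between-arm analysis names no therapy-group term, so its standard errors are too small if outcomes within a group are positively correlated

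*Protocol article*

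**What the plan says.** The Study design section labels the trial: "The design is a single-blind, parallel cluster RCT comparing MEST to an ES intervention". Participant allocation gives the unit: "Eligible participants will be cluster randomised using a blocked randomisation procedure with 5 to 8 participants in a group to receive the intervention". Both arms are delivered in such groups; the Education and support section describes that intervention as "delivered to groups of 5 to 8 individuals over five 60-minute sessions", and the MEST section gives the same group size.

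On numbers, Power analysis and sample size says that "60 participants (30 in each arm) will provide sufficient numbers to evaluate outcome, feasibility and acceptability" and then: "This sample size will give 24 patients in each arm if we allow for 20% attrition". It mentions no ICC or design effect.

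The Statistical analysis plan section names the method and the comparison: "Mixed model analyses of variance (ANOVAs) will be used to compare groups at the four assessment points". It adds baseline levels as covariates where appropriate, intention-to-treat and then per-protocol analyses, and mediation analyses. On missing data it says only: "Multiple imputation will be used to handle missing data". Therapy group, a random group effect, robust standard errors and a cluster-level test do not appear.

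**The concern.** In a cluster-randomised trial the evidence about the arm effect comes from the variation between randomised clusters. Here members of a group practise, share and discuss together over five sessions in both arms, so some correlation of their outcomes is plausible.

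A mixed ANOVA of arms across assessment points reads most naturally as arm (between participants) by time (within participants). A participant effect in such a model deals with the repeated measurements on one person. It does not deal with the correlation between people in the same therapy group. Followed as written, the analysis treats 48 to 60 people as independent when about 8 to 12 units were randomised.

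The comparisons affected are those between arms at post-treatment and at 3 months, the primary one among them, and the arm-to-mediator step of the mechanism study. Point estimates are not biased by leaving the term out; intervals and p-values are what suffer. That still counts. The Background asks whether MEST is superior to the control, the Discussion makes superiority one of the conditions for supporting a Phase III trial, and the sample size section intends to use the estimates to plan later trials.

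**Working it through.** **Inputs from the article**
- 60 participants, 30 per arm; groups of 5 to 8.
- 20% attrition. Reproduced: 30 × (1 − 0.20) = 24 per arm.

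**Assumptions, because the article gives no figure**
- Two-sided alpha of 5%.
- ICC of 0 to 0.15, shown as a range.

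**Number of clusters.** 60/8 = 7.5 and 60/5 = 12, so about 8 to 12 in all. Per arm, 30/8 = 3.75 and 30/5 = 6, so 4 to 6.

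**Group size as analysed.** With 24 per arm: 24/6 = 4 (six groups) to 24/4 = 6 (four groups).

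**Formulas**
- Design effect: DE = 1 + (m − 1) × ICC.
- Naive SE as a share of the true SE: 1/√DE.
- Actual type I error of an individual-level test: 2 × [1 − Φ(1.96/√DE)].

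Example, m = 6 and ICC 0.10: DE = 1 + 5 × 0.10 = 1.50; 1/√1.50 = 0.816; 1.96 × 0.816 = 1.60; type I error = 2 × [1 − Φ(1.60)] = 0.11.

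The formula was checked by simulation without a treatment effect (60,000 trials per setting), using an individual-level t-test.

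| Groups per arm × size | ICC | DE | Naive SE / true SE | Type I error, formula | Type I error, simulated |
|---|---|---|---|---|---|
| 6 × 4 | 0 | 1.00 | 1.00 | 5.0% | 4.9% |
| 6 × 4 | 0.01 | 1.03 | 0.99 | 5.4% | 5.4% |
| 6 × 4 | 0.05 | 1.15 | 0.93 | 6.8% | 6.9% |
| 6 × 4 | 0.10 | 1.30 | 0.88 | 8.6% | 8.5% |
| 6 × 4 | 0.15 | 1.45 | 0.83 | 10.4% | 10.5% |
| 4 × 6 | 0 | 1.00 | 1.00 | 5.0% | 5.0% |
| 4 × 6 | 0.01 | 1.05 | 0.98 | 5.6% | 5.4% |
| 4 × 6 | 0.05 | 1.25 | 0.89 | 8.0% | 8.0% |
| 4 × 6 | 0.10 | 1.50 | 0.82 | 11.0% | 11.2% |
| 4 × 6 | 0.15 | 1.75 | 0.76 | 13.8% | 14.5% |

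A t-test on therapy-group means, run on the same simulated data, rejected in 4.9% to 5.2% of trials in all these settings.

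**Degrees of freedom.** Number of groups − 2: 8 − 2 = 6 to 12 − 2 = 10, with critical t of 2.45 to 2.23. An individual-level test with 24 per arm uses 48 − 2 = 46, with critical t of 2.01.

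The simulation is of an unadjusted comparison at one time point, not of the full repeated-measures model. With baseline adjustment, the ICC that counts is the one left after adjustment.

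**The case against.** The strongest reply is that the omission is one of silence. The analysis section is a condensed paragraph, a mixed model can carry a random therapy-group effect, and a fuller analysis plan may specify one. This stands to the extent that nobody can say the trial team will ignore clustering. It does not remove the mismatch: the article names the method, the comparison and the covariates, and what it names fits individually randomised data, although the design is labelled cluster-randomised.

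A second reply is that the trial is exploratory and deliberately has no conventional power calculation, so point estimates are what it is after. That limits the harm to intervals and p-values. It does not dispose of it, given the weight that the Discussion puts on superiority.

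Several stronger readings are tempting and should be resisted:
- **The type I error certainly exceeds 5%.** This holds only for a positive ICC, which the article does not give. At ICC 0.01 the excess is about half a percentage point.
- **The imputation ignores therapy group and adds to the error.** The article gives no imputation model at all, so it shows neither that the group is left out nor that it is included.
- **Shared therapists add to the clustering.** The Treatment integrity section has the same two psychologists delivering both interventions, so therapist is not shown to be nested in arm. The argument rests on the shared group.
- **Every secondary outcome is affected.** The 6-month assessment is for the MEST arm only, so there is no between-arm test there to inflate.
- **Error rates as high as 17%.** At ICC 0.15, four groups of 8 per arm gives about that, but 4 × 8 × 2 = 64 people exceeds the planned 60 and allows for no attrition.

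**Conclusion.** The concern holds in a conditional form. The unit of randomisation is the therapy group, and the analysis as written does not account for it. With any positive ICC, the standard errors of the between-arm comparisons at post-treatment and 3 months, including the primary one, are too small.

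Under a nominal two-sided 5% test with 24 analysed per arm, the excess runs from negligible (about 5.5% at ICC 0.01) to a doubling or more (9 to 11% at ICC 0.10, 10 to 14% at 0.15). Alpha and ICC are assumptions here, and the size depends on them; the direction, for a positive ICC, does not. Because the primary comparison feeds the case for a Phase III trial, the text should be corrected before the data are analysed.

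**What to change.** In the Statistical analysis plan section, state that every between-arm model accounts for therapy group, by one of two routes:
- a random effect for therapy group, with Kenward-Roger or Satterthwaite degrees of freedom; or
- a t-test on baseline-adjusted group means, with (number of groups − 2) degrees of freedom.

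The second route deserves serious thought. With 8 to 12 clusters, the estimated between-group variance came out at or below zero in 35 to 40% of simulated trials at ICC 0.05, so a random effect would often vanish from the fitted model. Whichever route is taken, fix it in advance.

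State also that the imputation model will be compatible with this analysis, so that it preserves the correlation within therapy groups. Report the ICC with its interval. The interval will be wide, but later trials of group-delivered MEST will need the figure for planning.

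No change to recruitment, delivery or data collection is needed, provided that therapy-group membership is kept in the dataset. The cost is statistical: 6 to 10 degrees of freedom for the arm comparison (critical t of 2.45 to 2.23 rather than 2.01), wider intervals and less power. If a fuller analysis plan already contains such a term, the published text only needs to say so.
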